## 3. Data Plan Analyses

Data are analyzed using intention-to-treat principles. Descriptive data (means, standard deviation, and frequencies) are reported for all study variables. These include usability and acceptability and response rates in the app (primary outcomes), together with brace adherence, the number of side effects, the number and type of clinical alarms generated by the app, stress, quality of life, perceived health status, and mood (secondary outcomes). Statistical differences between completers and non-completers are calculated. Completers are those who respond to at least 85% of the requested daily assessments, which is the average completion rate in EMA revealed in past meta-analytic research [42]. Adolescents who provide less than 85% responses to the app are considered non-completers.

Regarding feasibility, app adherence is calculated by dividing the number of responses registered in the app and the number of assessments programmed in the app (90 assessments, once daily during the whole study).

In relation to the clinical utility of the app, brace adherence is calculated by dividing the number of hours of use reported by the prescription they were given, as suggested in previous research [43]. Low brace adherence serves as a clinical alarm (Table 1). Changes in the remaining secondary measures (i.e., stress, perceived quality of life, perceived health status, and mood) from baseline to end of study are also explored, although it is expected to find minimal changes because these are not the main aim of the present study.

The results derived from the statistical analyses described above will be reported in the form of tables, graphs, and flowcharts. All the analyses are performed separately by the lead researcher and an independent researcher. An interim analysis is planned at the end of the study once 50% of the total sample has been evaluated. All coauthors and the Ethics Committee of the Vall d’Hebron University Hospital have access to these analyses and are allowed to participate in the decision to terminate the trial. The database is available under reasonable request for any researcher who requests it. Personal information from the participants is not included in this data set. The results from this feasibility study will be published anonymously in international journals and conferences.

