## Abstract

Attempts to optimize monitoring of brace adherence prescribed to adolescents with idiopathic scoliosis (IS) have generally relied on sensors. Sensors, however, are intrusive and do not allow the assessment of psychological and physical consequences of brace use that might underlie poor adherence. Mobile applications have emerged as alternatives to monitor brace compliance. However, the feasibility and utility of these app-based systems to assess key psychological and physical domains associated with non-adherence remain unexplored. This feasibility study aims to test the usability, acceptability, and clinical utility of an app-based system that monitors brace use and related psychological and physical factors. Forty adolescents with IS daily respond to the app for 90 days. The patient responses may generate clinical alarms (e.g., brace non-adherence, discomfort, or distress) that will be sent daily to the medical team. Primary outcomes will be app usability, acceptability, and response rates. Secondary outcomes will include brace adherence, the number of side effects reported, number and type of clinical alarms, stress, quality of life, perceived health status, and mood. If accepted by patients and clinicians, apps may allow rapid detection and response to undesired events in adolescents undergoing brace treatment.

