It might be reasonable to think that the inclusion of an app-based monitoring system in clinical settings can help overcome the barriers of traditional, retrospective face-to-face assessments, and electronic devices (i.e., sensors and web pages). In the present study, we aim to test the feasibility and clinical utility of a new app-based management method. With this app, we intend to improve the monitoring of brace adherence, as well as the psychological and physical status of patients with AIS. Regarding feasibility, this study aims to explore the extent to which patients (adolescents with IS) and physicians accept the use of an app for daily monitoring. In relation to clinical utility, the objective of this work is to test whether the app detects adherence problems with the brace and related side effects and the clinicians respond quickly to them. We anticipate that the implementation of the app will be feasible for AIS monitoring (high acceptability and adherence to the app). In addition, we expect to find some indicators of the potential usefulness of the app (e.g., rapid detection of brace adherence problems and psychological and physical complications that allow a quick response by the medical team).

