Participants respond daily to the questions in the app. They are prompted in the afternoon (at 7 pm) and have 2 h to respond (until 9 pm). If participants do not respond to the assessment by 8:30 p.m., a second reminder is sent. If participants access the application after 9 p.m., they are not allowed to complete the daily assessment, which is treated as missing data, and participants are instructed to access to the app the next day at the scheduled time. This is done to avoid backfilling and non-ecological assessment. EMA involves the assessment of the current or very recent status of patients [30]. If participants were allowed to respond to the daily assessments later than 9 p.m., this would compromise the ecological nature and comparability of the assessments. After 3 days of app non-compliance, the app sends a notification to the doctors, and they will call the patients to encourage compliance with the app.

Clinical alarms are generated in the app according to certain preset unwanted events (see Table 1). Every working day, the physicians will receive an anonymous report that will contain only the alphanumeric code described above, together with the description of the alarm. Next, the physicians access the document where the alphanumerical code is linked with the medical record number (Appendix C) to check the clinical history of the patients and decide the type of action necessary to solve the clinical alarm. Clinical alarms are not an emergency service and patients should use the services they usually use (i.e., emergency services, primary care, call to the Physical Medicine and Rehabilitation Service, etc.) in case they are faced with any symptom that worries them.

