### 2.5. Outcome Measures

Primary outcome measures:The usability and acceptability of the app will be assessed by both patients (end users) and clinicians (relevant stakeholders). In the patients, this is evaluated both objectively and subjectively. To obtain an objective feasibility result, we calculate the adherence with the app by dividing the number of completed assessments by the number of planned evaluations and provide the response rate. To obtain a subjective measure of usability and acceptability, at the end of the study period (3 months after the first use of the app), we administer the System Usability Scale (SUS) [31] using an online survey tool that will be sent by mail (*Qualtrics*).In the clinicians, the acceptability of the new app-based monitoring method is evaluated using an assessment protocol developed for a similar earlier study [16]. As reported in Appendix D, this includes items that are consistent with the technology acceptance model [32], including perceived utility, acceptability, and intended use. This will be evaluated at the end of the study with the *Qualtrics* online survey tool anonymously.

Secondary outcomes measures:

Assessed by the Pain Monitorapplication (all once daily from 7 p.m. to 9 p.m.):
Brace adherence: Ad hoc self-reported item: “When have you been able to wear the brace since you went to bed yesterday?” Response options cover all daily periods (morning only, afternoon only, only for sleeping, or any combination of these). To avoid bias due to socially desirable responses, honesty will be encouraged both during recruitment and in the informed consent.Treatment safety: An ad hoc question has been created including the most frequent side effects of brace use according to the literature [10,12] and the authors’ clinical expertise. These include: pain due to pressure, pain due to friction, excessive heat/sweating, movement difficulties, and being teased by peers or close ones.Clinical alarms: in addition to the assessment of brace adherence and side effects, several items were adapted from validated questionnaires (Appendix D) to assess pain intensity, unpleasant emotions, interference, avoidance, discomfort, and social support daily. Clinical alarms will be automatically generated and sent to the physicians by the app depending on the patients’ responses to these items (Table 1).

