## Figures and Tables

**Figure 1 ijerph-18-07767-f001:**
[figure not shown]
Study timeline.

**Table 1 ijerph-18-07767-t001:** Pre-specified clinical alarms detected by the mobile application.

Domain	Clinical Alarms	Recommendations ^1^
Side effects		
Pressure pain	3 consecutive days	Call the patient
Friction pain	3 consecutive days	Call the patient
Excessive heat/sweating	7 consecutive days	Call the patient
Movement difficulties	3 consecutive days	Call the patient
Teased by peers/relatives	4 consecutive days	Psychoeducation
Pain		
Pain intensity	≥3 during 3 consecutive days	Call the patient
Emotions		
Sadness	5 consecutive days	Psychoeducation
Anxiety	5 consecutive days	Psychoeducation
Anger	5 consecutive days	Psychoeducation
Shame	5 consecutive days	Psychoeducation
Overwhelm	5 consecutive days	Psychoeducation
Frustration	5 consecutive days	Psychoeducation
Interference		
Sleeping	3 consecutive days	Call the patient
Basic movements	3 consecutive days	Call the patient
Relationships (friends)	5 consecutive days	Psychoeducation
Relationships (relatives)	5 consecutive days	Psychoeducation
Leisure activities	5 consecutive days	Psychoeducation
Academic activities	5 consecutive days	Psychoeducation
Mood	5 consecutive days	Psychoeducation
Dressing	5 consecutive days	Psychoeducation
Self-image	5 consecutive days	Psychoeducation
Motivation for going out	3 consecutive days	Psychoeducation
Avoid talking about the brace	≥7 during 7 consecutive days	Psychoeducation
Avoid activities/being with others	≥5 during 5 consecutive days	Psychoeducation
Overall physical discomfort	≥5 during 5 consecutive days	Call the patient
Brace adherence		
Morning only (8–14 h)	7 consecutive days	Call the patient
Afternoon only (14–19 h)	7 consecutive days	Call the patient
Sleeping only (last night)	7 consecutive days	Call the patient
Morning and afternoon only	7 consecutive days	Call the patient
Sleeping and morning	15 consecutive days	Call the patient
Sleeping and afternoon	15 consecutive days	Call the patient
No use of the brace	3 consecutive days	Call the patient
Poor social support		
Friends	5 consecutive days	Psychoeducation
Family	5 consecutive days	Psychoeducation
Teachers	5 consecutive days	Psychoeducation
Other people	5 consecutive days	Psychoeducation

^1^ The physician may change the recommended action according to the patient’s condition.

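### The daily safety outcome is summarised as a number of side effects, which, if summed over the 90 days, rises and falls with how often the patient answered

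*Protocol article*

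**What the plan says.** Section 3 (Data Plan Analyses) promises means, standard deviations and frequencies for all variables. Among the secondary outcomes it lists "the number of side effects, the number and type of clinical alarms generated by the app". The Abstract uses nearly the same terms: "the number of side effects reported, number and type of clinical alarms".

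Section 2.5 gives side effects their role: "Treatment safety: An ad hoc question has been created including the most frequent side effects of brace use". The question is a daily checklist of five types (pressure pain, friction pain, heat or sweating, movement difficulties, teasing), and Appendix D lets the patient tick more than one.

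Section 2.3 closes the response window at 9 p.m. For patients who open the app later, "they are not allowed to complete the daily assessment, which is treated as missing data".

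Section 3 does give a denominator to app adherence: "app adherence is calculated by dividing the number of responses registered in the app and the number of assessments programmed in the app", that is, 90. It gives one to brace adherence as well (the prescription). It states none for side effects. It also plans a comparison by response level: "Statistical differences between completers and non-completers are calculated", with completers defined by at least 85% of daily assessments answered.

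**The concern.** A side effect can be recorded only on an evening that was answered. A 90-day sum of reports therefore mixes two things: how often the problem occurred and how often the patient opened the app in time. Response is expected to vary between patients. It is itself a primary outcome, and the plan sets a threshold to separate high from low responders.

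What is at stake is how the trial's daily safety measure is read. A low number could mean a well-tolerated brace or only a patient who answered less. If completers and non-completers were compared on summed reports, part of any difference would come from the way the groups are defined.

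Refusing late entries is sound practice for momentary assessment and is not criticised here.

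**Working it through.** The plan gives no expected number of side effects, so there is no figure of its own to reproduce.

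**Inputs**
- From the protocol: n = 90 planned assessments; completer threshold 85%. Since 0.85 × 90 = 76.5, a completer has at least 77 answers and a non-completer at most 76.
- Assumed: daily probability q of a given side effect; response rates r of 100% and 70% beside the protocol's 85%; missed evenings unrelated to symptoms unless stated.

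**1. Reports summed over the study**

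Expected sum = n × r × q. With q = 0.50:

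| Response | Expected sum | Proportion of answered days |
|---|---|---|
| 100% | 90 × 1.00 × 0.50 = 45.0 | 0.50 |
| 85% | 90 × 0.85 × 0.50 = 38.25 | 0.50 |
| 70% | 90 × 0.70 × 0.50 = 31.5 | 0.50 |

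Two patients with the same daily risk, one at 100% and one at 70% response, differ by 45 − 31.5 = 13.5 reports.

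The order of patients can also reverse. A daily risk of 40% with 50% response gives 90 × 0.40 × 0.50 = 18.0 reports. A risk of 25% with 95% response gives 90 × 0.25 × 0.95 = 21.4. The patient at lower risk shows the higher number.

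**2. Number read as distinct types ever reported**

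Probability that a type is seen at least once = 1 − (1 − q·r)^90. For a rare type, q = 0.05, this is about 99%, 98% and 96% at 100, 85 and 70% response. On this reading the dependence on response is slight.

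**3. Does the proportion hold up if missed days relate to symptoms?**

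Take q = 0.50 and double the odds of missing on problem days (assumed).
- 85% response overall: missed 10.7% of good days and 19.3% of problem days. Proportion = (0.5 × 0.807) / 0.85 = 0.475. Sum = 45 × 0.807 = 36.3.
- 70% response overall: missed 22.8% and 37.2%. Proportion = (0.5 × 0.628) / 0.70 = 0.449. Sum = 45 × 0.628 = 28.3.

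The proportion falls short of the truth by 5% and 10% in relative terms; the sum falls short of 45 by 19% and 37%.

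A harsher case: q = 0.30, with 85% of good days but only 50% of problem days answered. Proportion = 0.15 / (0.15 + 0.595) = 0.20 against a true 0.30. Sum = 90 × 0.15 = 13.5 against a true 27. The proportion is clearly biased here, but less than the sum.

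**The case against.** The strongest reply is that the article names variables and does not fix an undivided 90-day total. Frequencies may include percentages, and the number of side effects may mean distinct types or a daily mean. A condensed article commonly leaves such details to a fuller document. Much of this stands: the point is conditional on summation, and under the distinct-types reading it nearly disappears. What remains is that the measure is named twice as a number, with no answered-day denominator stated. A types-only count would also discard the daily frequency that the app is there to collect.

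A second reply is that the response rate is reported anyway as a primary outcome. That helps, but separate group summaries do not let a reader match one patient's reports to that patient's answered days.

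A third is that stakes are low: 40 patients, one arm, a secondary descriptive outcome, no decision rule attached, and a Discussion that already urges caution about utility data. This is accepted and sets the severity.

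Two stronger readings are tempting, and the documents do not support either.
- *Alarm counts are wrong too.* Every row of Table 1 needs a run of days, up to "15 consecutive days", so missed evenings can change how many alarms fire. But the article does not say how a missed day affects a run or when an alarm fires again, and the direction depends on both. For a problem present every day under a 7-day rule, expected alarms at 100, 85 and 70% response are 12, 6.1 and 2.3 if a miss breaks the run and the counter resets after each alarm. They are 12, 10.5 and 8.6 if misses are skipped, and 1, 4.3 and 2.1 if the alarm fires once per unbroken run. Moreover, section 1 says "the objective of this work is to test whether the app detects adherence problems with the brace and related side effects" and that clinicians respond. Alarms actually sent are the right record of system output and workload.
- *The completer comparison is biased.* Section 3 does not name the variables to be compared. Nothing says that raw side-effect counts will be tested.

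**Conclusion.** The point holds in a limited form. If side-effect reports are summed over 90 days, the safety summary is proportional to the response rate: 45, 38 and 32 reports at 100, 85 and 70% response for the same true burden. These figures assume a side effect on half of days and misses unrelated to symptoms; the 100% and 70% rates are also assumed. If the number means distinct types ever seen, the effect is a few percentage points even for a rare type.

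This is a low-severity improvement to a stated summary measure. It is neither a contradiction in the plan nor a threat to its primary outcomes. No error is claimed for the alarm counts, and the completer comparison is affected only if it turns out to use raw side-effect counts.

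**What to change.** Add two or three sentences to section 3:
- For each patient and each side effect, also report the proportion of answered days on which it was present, with the number of answered days beside it.
- If completers and non-completers are compared on side effects, use this proportion, not the raw count.
- Keep alarm counts as fired, as the measure of system output and clinician workload, and show them beside the response rate. Alarms need no recomputation.
- State that the proportion assumes missed evenings are unrelated to symptoms, and that it would understate the burden if patients miss more on bad days.

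The cost is slightly more tabulation from data already in the app log. The app does not change. The residual weakness is the bias shown above: a true 50% would read about 47% at 85% response and 45% at 70% if the odds of missing doubled on problem days.

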### 2.3. Usual AIS Treatment + App-Based Ecological Momentary Assessment

In addition to the app, all adolescents receive the usual treatment for scoliosis that is provided in the Physical Medicine and Rehabilitation Service during the study period (90 days), that is, they are prescribed the daily use of a brace. In terms of monitoring, routine practice in the unit only includes a face-to-face assessment 3 months after the final version of the brace is prescribed, which means that problems with this final version of the brace are traditionally assessed retrospectively. Therefore, to minimize the problems associated with relying only on retrospective and episodic evaluations, the present study incorporates a daily app-based monitoring during 90 days since the start of brace treatment, which is a critical period in which the physical and psychological adaptation to full-time use of the brace might be more challenging.

The Pain Monitor app is a mobile application whose contents have been adapted to conduct ecological momentary assessments (EMA) in different health conditions. It has been previously validated in chronic pain conditions [29] and has received several awards since then (https://www.consalud.es/saludigital/145/premios-saludigital-2019-reconocen-mejores-iniciativas-tecnologia-sanitaria_60524_102.html, accessed on 11 July 2021). It is currently available for free in the Android (https://play.google.com/store/apps/details?id=monitorinvestigacion.code, accessed on 3 July 2021) and iPhone (https://apps.apple.com/es/app/monitor-de-dolor-multic%C3%A9ntrico/id1546241257, accessed on 3 July 2021) stores. The app evaluates important brace-related physical and psychological domains, namely side effects of the brace, pain intensity, mood, brace interference, brace adherence, avoidance behavior, discomfort, and social support. Following the procedure of a similar investigation [29], to create the EMA assessment protocol, a multidisciplinary team of psychologists and physicians revised the most frequent assessment tools in the AIS literature and selected the most representative constructs to create a representative, but short set of items (see a detailed description in Appendix D).

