To what extent the app is useful for me as a professional?

To what extent the app can be useful for patients with IS?

To what extent the app with alarms is something I want to use in the future?

To what extent the app without alarms is something I want to use in the future?

To what extent the app alarms impacted daily job burden?

To what extent the app has an impact on burden (help patient downloading the app)?

2. **Items Assessed with the Pain Monitor Mobile Application**

A number of items were adapted from or developed considering well-established questionnaires (e.g., BSSQ, ISYQOL, SRS-22, HADS) in order to assess relevant brace-related domains namely side effects of the brace, avoidance behavior, discomfort, and social support.

Items assessed daily at evening

Please indicate if any of these possible consequences of the brace have been difficult for you to bear TODAY. You may select more than one option: (*Inspired by the SRS-22 and the ISYQOL*)

Pressure pain

Friction pain

Excessive heat/sweating

Movements difficulties

Teasing by peers or relative ones

None of the above have difficult for me today

Please indicate the intensity of your pain TODAY. Indicate the average for the whole day between 0 and 10. (*Inspired by the SRS-22*)

0 No pain ---------10 Extreme pain

Please indicate if you feel some of these intense emotions TODAY due to bracing. You may select more than one option: (*Inspired by the SRS-22 and the HADS*)

Sadness

Anxiety

Anger

Shame

Overwhelm

Frustration

I did not feel any of these emotions intensely because of the brace

Please indicate if brace have interfered you in some of these aspects TODAY. You may select more than one option: (*Inspired by the SRS-22, the ISYQOL, and the BSSQ*)

Sleeping (last night)

Basic movements

Friends’ relationships

Family’ relationships

Leisure activities

Academic activities

Mood

Dressing

Self-image

Motivation for going out (classroom or leaving home)

None of the above have disturbed me today

When have you been able to wear the brace sin you went to bed yesterday? [Item created to assess de degree of nonadherence (mildly vs. severe nonadherent), as recommended by [51]

Only at morning (8–14 h approx)

Only at afternoon (14–19 h approx)

Only for sleeping (last night)

Today at morning and afternoon, but no for sleeping (last night)

Sleeping (last night) and this morning

Sleeping (last night) and this afternoon

Sleeping (last night) and all day

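### Read plainly, Table 1 gives each wear answer its own run of days, so a worse day ends the run and a patient who keeps switching can raise a brace-adherence alarm late or never

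*Protocol article*

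**What the plan says.** Section 3 (Data Plan Analyses) defines brace adherence as reported hours over prescribed hours, then states "Low brace adherence serves as a clinical alarm (Table 1"). Under Brace adherence, Table 1 has seven rows, one for each daily wear answer in Appendix D except "Sleeping (last night) and all day". The counts of consecutive days are:

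- 3 for "No use of the brace";
- 7 for morning only, afternoon only, sleeping only, and morning with afternoon;
- 15 for "Sleeping and morning" and for sleeping with afternoon.

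No row or sentence pools answers, counts low-wear days cumulatively, or triggers on the hours/prescription ratio. The footnote, "The physician may change the recommended action", concerns the response and not the trigger. The 3-day notice in section 2.3 is about not answering the app.

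Section 1 expects "rapid detection of brace adherence problems", and section 4 hypothesizes early detection of low brace adherence. Section 2.3 says "the physicians will receive an anonymous report that will contain only the alphanumeric code described above, together with the description of the alarm", and that "routine practice in the unit only includes a face-to-face assessment 3 months after the final version of the brace is prescribed".

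**The concern.** The seven answers are mutually exclusive. If each has its own run, a change of answer restarts the count whether wear improved or worsened. The rule then does not follow severity: a patient who wears the brace less can go unflagged while one who wears it more is called.

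Without an alarm the physician receives nothing about that patient's wear. Unless a pain, discomfort or interference alarm happens to fire, low wear goes unflagged until the retrospective 3-month visit that the app is meant to improve on. The number and type of alarms is also a reported secondary outcome, so a low adherence-alarm count could be misread as good adherence.

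**Working it through.** **Inputs.** Thresholds of 3, 7 and 15 days (Table 1); 90 daily assessments (section 3); a full-time prescription (section 2.2), given as 20–24 h (section 1); morning slot 8–14 h = 6 h and afternoon slot 14–19 h = 5 h (Appendix D). Assumed: 8 h of sleep, and no full-wear or missed days unless stated. The article gives no alarm rate to reproduce.

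**Fixed patterns under Table 1**

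| Repeated pattern | Mean wear | Share of 20–24 h | First adherence alarm |
|---|---|---|---|
| Sleeping only, every day | 8 h | 33–40% | day 7 |
| 2 no use, 1 sleeping only | 8/3 = 2.7 h | 11–13% | none in 90 days |
| 5 sleeping only, 2 no use | 5 × 8/7 = 5.7 h | 24–29% | none |
| 14 sleeping+morning, 14 sleeping+afternoon | (14 + 13)/2 = 13.5 h | 56–68% | none |

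In the second row the brace is off on 60 of 90 days. The third row depends on day order: the same 5:2 mix in random order alarms with probability 99.4%.

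**Switching patients.** Let p be the chance of repeating yesterday's answer, with the rest split equally among the other answers. An exact recursion on (answer, run length), stopping when a run reaches its threshold, gives the chance of any adherence alarm. For equal use of sleeping only, sleeping+morning and sleeping+afternoon, mean wear is (8 + 14 + 13)/3 = 11.7 h, or 49–58% of prescription:

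| p | by day 30 | by day 90 |
|---|---|---|
| 1/3 (independent days) | 0.7% | 2.5% |
| 0.5 | 6% | 20% |
| 0.6 | 16% | 44% |
| 0.7 | 31% | 72% |
| 0.8 | 54% | 93% |
| 0.9 | 82% | 99.8% |

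For equal use of all seven answers, the 90-day chance is 20% (independent), 89% (p = 0.5) and 99% (p = 0.7).

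**Equal-or-worse counting.** No use counts toward every run, the four 7-day answers count toward the 7- and 15-day runs, and the two 15-day answers count toward the 15-day run. The three unflagged patterns above then alarm on days 7, 7 and 15. Any patient who answers daily and never reports full wear alarms by day 15.

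**Its limits.** The table gives the 90-day alarm chance for the three-answer model, from independent days to p = 0.8:

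| Added days | Table 1 as printed | Equal-or-worse |
|---|---|---|
| 10% full wear | 1–73% | 94–97% |
| 20% full wear | 0.6–46% | 47–67% |
| 30% full wear | about 0.3–24% | 11–31% |
| 15% missed, run reset | 1–60% | 74–86% |
| 15% missed, run paused | not calculated | 100% |

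Two days of no use then one of full wear, repeated, still never alarms. With pausing, a completer (85% of 90 = 76.5, so at least 77 answers and at most 13 missed) with no full-wear day alarms by day 15 + 13 = 28.

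**Duplicate alarms.** Suppose each count restarts only after its own alarm. A steady no-use patient has 90/3 = 30 alarms under Table 1. Equal-or-worse counting adds 12 seven-day and 6 fifteen-day alarms, making 48. A steady sleeping-only patient goes from 12 to 12 + 6 = 18. If the shortest threshold met also restarts the longer counts, the totals return to 30 and 12.

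**The case against.** Table 1 is a summary in a journal article, and the article does not say outright that rows are never pooled. The app's code may do so. That stands, so this is a reading of the table, although separate rows with different counts favour it.

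The affected group is narrow and its size unknown. If wear follows a daily routine, persistence is high and the 90-day gap nearly closes. That also stands. Even at p = 0.9, though, 18% of the modelled patients have no alarm by day 30.

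The 15-day counts suggest deliberate tolerance of partial wear, and alarm burden is itself assessed in Appendix D. A more sensitive rule could be called a different preference. This stands for the choice of thresholds, but not for letting a worse day cancel a run. The change proposed keeps the sponsor's thresholds.

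A reader might infer that the alarms generally miss poor adherence. The documents do not support that: steady patterns are caught on schedule, and so are most patients dominated by one low-wear answer unless their days fall in a fixed order. A reader might also infer that the adherence results or the feasibility conclusions are biased. They are not. Usability, acceptability and response rate do not use the alarms, and hours/prescription is calculated separately. Section 4 already asks for caution over the clinical-utility data.

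**Conclusion.** The point holds as a weakness in the alarm rule as printed: it is not ordered by severity, and frequent switching can delay or prevent a brace-adherence alarm. That much follows from the plain reading of Table 1 alone. Its frequency cannot be fixed from the documents. Under the three-answer model, 90-day detection ranges from 2.5% to 99.8% across the persistence levels shown, with late alarms over most of that range. The harm is to real-time detection and to using the alarm count alone as evidence of early detection. The change is worth making because early detection is a stated hypothesis and the remedy is cheap, but nothing primary depends on it.

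**What to change.** 1. Keep the 3-, 7- and 15-day thresholds, and state that any equal-or-worse day counts toward a run. State that a missed day pauses the run and does not reset it. Send one adherence alarm per episode, with the shortest threshold met restarting the longer counts, so that patients already caught do not generate duplicates. If the app already pools answers, one sentence saying so settles this part.
2. Because a full-wear day still resets the run, also report from data already collected the number of non-full-wear days per patient. Cross-tabulate hours/prescription, split at a cut-off that the clinical team states in advance, against whether any brace-adherence alarm was raised.

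The cost is a small app configuration change, some extra calls and one clinical cut-off. A switching patient who never has a no-use or 7-day answer would raise at most 90/15 = 6 alarms, the same ceiling that a steady sleeping+morning patient already has.
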